### Data management

All data will be stored in a digital research environment (myDRE, anDREa, Nijmegen, The Netherlands) for at least 15 years, adhering to the General Data Protection Regulation, Good Clinical Practice and Good Laboratory Practice guidelines. Standard software packages will be used for data handling and statistical analyses (eg, Castor EDC, IBM SPSS, R, Microsoft Excel). A comprehensive data catalogue is presented in table 2. In line with open science and the findable, accessible, interoperable and reusable (FAIR) principles, inquiries for reuse of the ENRICHED data can be directed to the corresponding author.

**Table 2 T2:** Data catalogue table of the ENRICHED study

Category	Subcategory	Variables
Baseline characteristics	Study inclusion	Allergic or sensitive to dairy proteins, or lactose intolerant (yes/no); diagnosed renal insufficiency (yes/no); diagnosed intestinal disease influencing uptake of protein (yes/no); inability to perform any resistance exercises (yes/no); previous MBS (yes/no); presence of medical devices which are contraindicated for BIA (yes/no); age >18 (yes/no); MBS scheduled (yes/no); able to understand and perform study procedures (yes/no); inclusion criteria met (yes/no); informed consent signed (yes/no); date of informed consent (dd-mm-yyyy).
	Demographics	Year of birth (yyyy); sex (female/male); medical history (text); Charlson Comorbidity Index (none/myocardial infarction/congestive heart failure/peripheral vascular disease/cerebrovascular disease (CVA or TIA)/dementia/chronic pulmonary disease/peptic ulcer disease/mild liver disease/hemiplegia/moderate-to-severe chronic kidney disease/tumour without metastasis/tumour with metastasis/leukaemia/lymphoma/HIV or AIDS/connective tissue disease/diabetes without organ damage/diabetes with organ damage/other (text).
	Randomisation	Intervention or control group (intervention group/control group); subgroup (yes/no).
Surgery	Surgery characteristics	Date of surgery (dd-mm-yyyy); type of surgery (RYGB/SG).
Measurements	Visit information	Date of visit (dd-mm-yyyy).
	Exercise characteristics	Do you usually do muscle-strengthening exercises (yes/no); if yes: how many days, in a usual week, do you do muscle-strengthening exercise (0/1/2/3/4/5/6/7); and: which type of muscle-strengthening exercise do you do (holistic exercises/body weight exercises/resistance band or free weights/weight machines)?

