### Sample size

Sample size calculation is based on the primary outcome of FFML/TWL ≥30% at 3 months post-MBS. The power analysis was based on differences between two independent groups (intervention group vs control group). We consider our intervention successful if we find an expected difference in prevalence of disproportional FFML of 26%^5^ versus 14% between the control and intervention group, respectively. Based on a two-sided test with α=0.05 and a power of 80%, 174 participants per study arm are needed to show this difference. Accounting for a 10% drop-out rate, a total of 400 participants will be recruited (200 per study arm). Calculations were performed using G-power V.3.1.2. (University of Düsseldorf, Düsseldorf, Germany)

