### Statistical analysis

Statistical analyses will be performed using R. Collected data will be checked for completeness and normality. Continuous parametric data will be displayed as mean±SD, non-parametric data as median (IQR) and categorical data as frequency with percentage. All statistical tests will be two-sided, and significance is set at p<0.05.

Descriptive analyses will be performed to explore the variance in the study parameters and calculate the baseline characteristics of the study population. For the primary analysis, an intention-to-treat approach will be used. Generalised estimating equations will be used for dichotomous outcomes grouped by patient ID to account for repeated measurements, including an adjustment for NOK centre and, if possible, adjusted for the baseline value of the outcome variable. A similar approach will be used for continuous outcomes using linear mixed-models analyses with a random intercept for patient ID to account for repeated measurements. The intervention effects will be evaluated for all follow-up time points by including a dummy variable for each time point and repeating the analyses with a different reference time point. Potential effect modification will be evaluated for sex, age group (age <50 years and age ≥50 years), type of surgery, study site and postmenopausal status (in female participants). A variable is treated as an effect modifier when its interaction term with the independent variable has a p value <0.10. When effect modification is observed, stratified results will be reported in addition to the overall results. Additionally, confounding will be evaluated for sex, age, baseline BMI, treatment adherence and type of surgery by including each variable in the model separately. Sensitivity analyses will be conducted to assess the robustness of the findings.

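### Effect modification by age is tested only with age split at 50; if the effect changes roughly linearly with age, the split loses about a third to a half of the information in that secondary test

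*Protocol article*

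**What the plan says.** The Statistical analysis section of the protocol article names five potential effect modifiers: sex, age, type of surgery, study site and, in women, menopausal status. Age enters as "age group (age <50 years and age ≥50 years".

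The decision rule is "A variable is treated as an effect modifier when its interaction term with the independent variable has a p value <0.10", and the consequence is "When effect modification is observed, stratified results will be reported in addition to the overall results".

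Three other statements bear on the choice:

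- The data catalogue (Table 2, under Data management) records "Year of birth (yyyy", so age to about one year is held for every patient.
- The same Statistical analysis paragraph says that "confounding will be evaluated for sex, age, baseline BMI, treatment adherence and type of surgery". Age is named there without grouping.
- Menopause has its own modifier, "postmenopausal status (in female participants".

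No reason is given for a cut at 50. The article reports no mean, SD or share of patients aged 50 or over, and it does not power any interaction test.

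**The concern.** Cutting a variable that is known to the year into two groups treats everyone from 18 to 49 as alike and separates a 49-year-old from a 50-year-old. If the benefit of training and protein changes gradually with age, the two-group comparison sees only part of that trend.

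The trial is sized for its main effect, so an interaction test starts with limited power. The lenient 0.10 threshold suggests that the authors want sensitivity, and the split works against that. When the rule is met, results reported on either side of 50 can also make a gradual trend look like a step.

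At stake is how well the trial can say whether the effect depends on age. The main result is not at stake.

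**Working it through.** **The plan's own figure.** The Sample size section expects 26% "versus 14% between the control and intervention group, respectively", with two-sided alpha 0.05 and 80% power. The usual two-proportion formula with pooled variance and no continuity correction is

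n = [1.960·√(2·0.20·0.80) + 0.842·√(0.26·0.74 + 0.14·0.86)]² / 0.12² = 173.2, rounded up to 174 per arm.

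This matches the stated 174. Power at 174 is 80.2%. Dividing by 0.90 for drop-out gives 194 per arm, which the planned 200 covers. The calculation concerns the main effect only.

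**Information kept by a split.** Assume normally distributed age and an interaction linear in age. The share of information kept is the squared correlation between age and the indicator of age 50 or over:

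RE = φ(c)² / [p(1 − p)], with c = (50 − mean)/SD and p = 1 − Φ(c).

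Mean and SD are assumptions; the cut at 50 is from the plan. To express the loss as power, take a continuous-age test with 80% power at the plan's 0.10 level. The 80% is also an assumption, chosen as a reference point. The split then has

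power = Φ[(1.645 + 0.842)·√RE − 1.645].

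| Assumed mean (SD 11) | c | Share ≥50 | Kept (RE) | Lost | Power, from 80% |
|---|---|---|---|---|---|
| 50 | 0 | 0.500 | 0.637 | 36% | 63% |
| 45 | 0.455 | 0.325 | 0.590 | 41% | 60% |
| 43 | 0.636 | 0.262 | 0.549 | 45% | 58% |
| 40 | 0.909 | 0.182 | 0.469 | 53% | 52% |

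Example for mean 40: φ(0.909) = 0.2639, so RE = 0.2639² / (0.182 × 0.818) ≈ 0.469 and power = Φ(2.487 × 0.685 − 1.645) = Φ(0.058) ≈ 52%.

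**Other assumed age distributions, still with a linear interaction.**

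- Uniform 20 to 70: 28% lost.
- Uniform 18 to 65: 35% lost.
- Normal truncated to 18 to 70 (mean 40 to 45, SD 11 or 12): 39% to 50% lost.
- Normal, mean 40, SD 10: 56% lost.
- Normal with 15% aged 50 or over: 57% lost.

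A still smaller share aged 50 or over would push the loss higher (66% at 10%), so 28% to 57% describes the inputs tried and is not a bound. Rounding age to whole years changes the loss by less than 0.1 percentage point.

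**Simulation of the binary outcome.** A logistic model was used with N = 348 (2 × 174), rates of 26% and 14% at the mean age, an assumed interaction of 0.6 log-odds per SD of age, a 0.10 threshold and 800 runs. It was run for mean/SD of 50/11, 45/12 and 40/11.

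| True shape | Continuous linear age: power | Split at 50: power |
|---|---|---|
| Linear in age | 68% | 49% to 52% |
| Step at 50 | 52% to 61% | 67% to 81% |

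Under the linear shape the split lost 37% to 42% of the information. Under a step at 50 the order reverses.

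**Spline alternative.** Take the same signal (80% power on 1 df at 0.10) and a truly linear trend. A 2-df spline interaction has about 71% power and a 3-df one about 65%. The latter is close to the 63% of a median split.

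**The case against.** The strongest reply is that the choice is defensible. The cut is pre-specified, so it is not driven by the data. The 0.10 rule is already lenient. Stratified results appear only when that rule is met, and then alongside the overall results. Two age groups also fit a plan that reports modification as strata. All of this stands and limits the consequence, but pre-specification does not recover lost information.

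It is also fair to say that the article does not establish the shape of any age effect. If it is a step at 50, the split wins. That stands too. The article offers no evidence for a step there, and equally none for a straight line, so the loss has to be stated as conditional.

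A flexible model would not be a free improvement. The plan's rates imply only about 70 primary events at 3 months (174 × 0.26 + 174 × 0.14 ≈ 70), and a multi-df spline gives back much of the gain. This rules out a spline as the main test.

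Three stronger readings are tempting and are not supported:

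- A reader might take 36% to 53% as a fact about this trial. It needs normal age, 18% to 50% of patients aged 50 or over, and a linear interaction, none of which the article gives.
- A reader might infer that 50 is a redundant stand-in for menopause, because menopausal status is tested separately. The article gives no reason for the cut, and the menopause modifier covers women only.
- A reader might infer that the main result is weakened. It is not affected.

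**Conclusion.** The point holds in a conditional form. The article fixes the age modifier as two groups although age is available to the year and is listed ungrouped as a confounder in the same paragraph. The grouping is therefore a choice and not a limit of the data. If modification is roughly linear in age, the loss is about a third to a half of the information in this one test, with the ranges and power figures worked out above. If the effect steps at 50, there is no loss.

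Nothing here is a contradiction or a miscalculation. The test is one of five secondary modifier checks. The primary comparison, its type I error and the 174 per arm are unaffected, so this is a low-priority improvement.

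**What to change.** In the Statistical analysis section, make the pre-specified age test the treatment-by-age interaction with age as a single continuous linear term (1 df), under the existing 0.10 rule. Check linearity as a sensitivity analysis only. Report the model-based intervention effect with 95% CI at a few stated ages, for example 30, 40, 50 and 60, and expect wide intervals at the extremes. Keep the results below and from 50 as a descriptive display.

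The cost is a sentence or two of analysis wording, with no new data and no change in N. The downside is a linearity assumption, and lower power than the planned split if the true effect is a step at 50. If the sponsor has a reason to expect such a step, stating it would justify keeping the split as the test.

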### Study setting and recruitment

This study is currently being conducted at two centres of the Nederlandse Obesitas Kliniek (NOK, Dutch Obesity Clinic), located in Nieuwegein and Amsterdam, in the Netherlands. The NOK consists of a national network of 10 sites throughout the Netherlands which provide a perioperative care programme for patients undergoing MBS. Patients qualify for the perioperative care programme in accordance with the International Federation for the Surgery of Obesity and Metabolic Disorders criteria; body mass index (BMI) ≥40 kg/m^2^ or BMI ≥35 kg/m^2^ in combination with obesity associated diseases (eg, type 2 diabetes or hypertension).^20^ Both Roux-en-Y gastric bypass (RYGB) and sleeve gastrectomy (SG) procedures are included in this trial to enhance generalisability of our findings and to allow examining whether the intervention is effective across both surgical techniques.

Recruitment of participants began in May 2025 and is expected to continue until December 2026. Patients are verbally informed about the study by the treating healthcare professional during the intake consultation at the participating centres. If patients provide their permission to be contacted for further information, a member of the research team evaluates eligibility via the electronic health record and contacts the patients to discuss potential participation. Inclusion and exclusion criteria are summarised in table 1.

**Table 1 T1:** Inclusion and exclusion criteria

Inclusion criteria	Exclusion criteria
Scheduled to undergo RYGB or SG in one of the participating centres.	Allergic or sensitive to milk proteins, or lactose intolerant.
Age ≥18.	Diagnosed renal insufficiency (ie, eGFR <30 mL/min).
Able to understand and perform the study procedures.	Diagnosed intestinal diseases influencing uptake of protein (ie, active inflammatory bowel disease, Crohn’s disease).
	Inability to perform any resistance exercises (eg, severe physical limitations).
	Previous metabolic–bariatric surgery.
	Presence of medical devices (ie, pacemaker, neurostimulator) which are contraindicated for bioelectrical impedance analysis.

eGFR, estimated glomerular filtration rate; RYGB, Roux-en-Y gastric bypass; SG, sleeve gastrectomy.

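### Stratified results, including those for the two surgical procedures, are promised only by way of an interaction p<0.10, which is a poor gate for reporting

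*Protocol article*

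**What the plan says.** The Statistical analysis section of the protocol article names the candidates: "Potential effect modification will be evaluated for sex, age group (age <50 years and age ≥50 years), type of surgery, study site and postmenopausal status", the last in female participants. It sets a decision rule, "A variable is treated as an effect modifier when its interaction term with the independent variable has a p value <0.10", and a reporting rule, "When effect modification is observed, stratified results will be reported in addition to the overall results". The general significance level is 0.05 two-sided, so 0.10 is specific to the interaction tests.

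The Study setting and recruitment section gives two reasons for including both gastric bypass (RYGB) and sleeve gastrectomy (SG): generalisability, and "to allow examining whether the intervention is effective across both surgical techniques".

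The Sample size section covers the overall comparison only. It assumes an "expected difference in prevalence of disproportional FFML of 26%^5^ versus 14% between the control and intervention group, respectively".

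**The concern.** One p value does two jobs: it decides whether a variable counts as an effect modifier, and it triggers the stratified results. Two things follow.

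First, with five variables each screened at 0.10, a chance flag is common, and the strata then shown are those that chance has selected.

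Second, whether the intervention is effective in both procedures is a question about the effect within each. It needs an estimate and a confidence interval for RYGB and another for SG. A non-significant interaction does not answer it, because failing to detect a difference does not show benefit in both. Yet that is the case in which the article makes no commitment to procedure-specific estimates.

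At stake is the completeness of the subgroup reporting, not the main result.

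**Working it through.** **The plan's own figure.** Two proportions, pooled variance under the null, two-sided 0.05, 80% power, mean proportion 0.20:

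n = [1.960·√(2·0.20·0.80) + 0.842·√(0.26·0.74 + 0.14·0.86)]² / 0.12² = 173.2, so 174 per arm. The stated figure is reproduced. With 200 recruited per arm and 10% dropout, 200 × 0.9 = 180 per arm are analysed, which is the number used below.

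**Chance flags.** Inputs: five variables and threshold 0.10, both from Statistical analysis.

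- Independent tests: 1 − 0.9⁵ = 0.410. Expected number of false flags: 5 × 0.10 = 0.5.
- The tests are not fully independent, since menopausal status tracks age and is tested in women only. A null simulation (360 patients, 4,000 replicates per setting) assumed 70–80% women, 25–50% aged 50 or over, 50–80% RYGB and two equal sites. It assumed 70% of the older and 5% of the younger women to be postmenopausal. At least one flag occurred in 37.5%, 37.8% and 39.6% of replicates in the three settings.

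So the rate is about 38–41% for one analysis of a given outcome.

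**Chance of flagging a real difference between procedures.** Assumptions, not in the document: the RYGB:SG split, and the planned effect (26% to 14%) in one procedure with none (26% to 26%) in the other. Wald test on the log-odds scale, two-sided 0.10 (critical value 1.645):

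- θ = logit(0.14) − logit(0.26) = −0.769
- Var = Σ 1/[n·p·(1−p)] over the four arm-by-procedure cells
- Power = Φ(|θ|/SE − 1.645) + Φ(−|θ|/SE − 1.645)

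At 50:50 each cell has 90 patients. Var = 3 × 1/(90·0.1924) + 1/(90·0.1204) = 3 × 0.05775 + 0.09228 = 0.2655, so SE = 0.515, |θ|/SE = 1.49 and power = 44%.

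| Procedure split | Effect only in the larger group | Effect only in the smaller group |
|---|---|---|
| 50:50 | 44% | 44% |
| 70:30 | 41% | 38% |
| 80:20 | 35% | 31% |
| 90:10 | 25% | 22% |

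The range is 22–44%, so the difference would go unflagged in 56–78% of such trials. With all 200 per arm analysed the range is 23–47%. If the second procedure has half the effect (26% to 20%), a flag appears in 14–21% of trials at 180 per arm.

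**Would another threshold help?** Five tests at 0.05 give 1 − 0.95⁵ = 22.6% for at least one chance flag, but the chance of flagging the one-procedure effect falls to 14–32%. Tightening the threshold trades one problem for the other, so the remedy is to stop using it as the gate.

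**The case against.** The approach is largely conventional. The modifiers are named in advance, age has a fixed cut-point, formal interaction tests are used, and 0.10 is a common concession to their low power. The overall result is always reported. Surgery-specific efficacy is not a listed outcome, the trial was not sized for it, and the interaction test does examine procedure. All of that stands and keeps this point minor. Error control and exploratory labelling may also sit in an analysis plan that is not shown, so their absence is not counted here.

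A reader might infer more than the text supports:

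- *Procedure-specific results will be withheld unless flagged.* The reporting rule contains no such exclusion. It says when strata will be reported and is silent on the other case. The supportable statement is that they are not promised.
- *The rule is applied at every visit and for every outcome, so false flags multiply.* Fifteen independent tests (five variables at three visits) would give 1 − 0.9¹⁵ = 79%. But the article speaks of a single interaction term per variable. Its sentence on time points, "The intervention effects will be evaluated for all follow-up time points by including a dummy variable for each time point", concerns intervention effects, not modification tests. Repeated measures are also correlated, so the 79% should not be used.
- *The 0.10 threshold is a mistake.* It is not; its use as a reporting trigger is the weakness.
- *The two sections contradict each other.* They do not. The analysis examines procedure, but the reporting commitment falls short of what the stated purpose needs.

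**Conclusion.** The point holds as a minor weakness in reporting. Following the rule as written, the trial could present strata picked out by chance and omit the RYGB and SG estimates that bear on one of its reasons for enrolling both procedures.

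The 41% assumes independent tests, and the simulated 38–40% rests on assumed patient characteristics. The 22–44% rests on an assumed procedure split, an all-or-nothing effect and a single-visit analysis at 3 months. A repeated-measures model could change it somewhat. At an even split the non-flag rate (56%) is only a little above one half, so the stronger statement that a real difference would nearly always be missed is not supported.

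**What to change.** For the primary outcome at 3 months, report the treatment effect with 95% CI in each pre-specified subgroup, at minimum RYGB and SG, together with the interaction estimate and its p value, whatever that p value is. Label these analyses exploratory, and do not use p<0.10 to decide what is reported.

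The cost is a change of wording and one table or forest plot. The estimates will be imprecise. On the risk-difference scale with 26% and 14%, the 95% CI half-width is 1.96·√[(0.1924 + 0.1204)/n]. That is about ±12 percentage points for n = 90 per arm (50:50 split) and about ±26 points for n = 18 per arm (smaller group at 90:10). The intervals make that uncertainty visible. The primary analysis and the sample size do not change.

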### Standard care

The standard perioperative care programme is focused on supporting patients in adopting a new healthy lifestyle incorporating mental and physical health. The objectives of the programme are to provide guidance to enhance adherence to healthy lifestyle and behaviour changes, ensure understanding of the benefits of a healthy lifestyle and improve both physical and mental health. The programme is provided by a multidisciplinary team consisting of bariatric physicians, dietitians, psychologists, kinesiologists, surgeons and internists. The programme consists of group sessions with up to 10 patients per group; each group is assigned to one of the healthcare professionals who functions as coach. Preoperatively, patients participate in group sessions on a weekly basis for 4 weeks. Postoperatively, the group sessions are repeated every 3–6 weeks for a 15-month period. In addition, medical checks are performed by a bariatric physician at 3 weeks postsurgery and repeated every 3 months, up to 1 year post-MBS.

Allocation to our control group does not restrict participants from engaging in RT or consuming additional protein. This is emphasised by the research team during recruitment. Moreover, the research team is trained to ensure equipoise delivery during recruitment by presenting both study arms as equally important for the aim of this study.

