### Intervention

The ENRICHED intervention consists of two consecutive phases, starting 3 weeks after surgery and continuing for a total of 24 weeks (figure 1). Phase 1 (3–14 weeks post-MBS) focuses on home-based and supervised RT and gradually increasing protein supplementation. Phase 2 (15–26 weeks post-MBS) continues with the same RT protocol while transitioning from protein supplementation to enhancing dietary protein intake.

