#### Protocol adherence

For participants in the intervention group, adherence to the RT protocol will be monitored via the Technogym application (Technogym, Cesena, Italy), which allows participants to log both completion of the home-based and supervised RT sessions. Additionally, adherence to the home-based RT protocol will be assessed using an online single question survey (Castor EDC, Castor). Attendance at the supervised RT sessions will be recorded using an attendance list. Adherence to the whey protein supplementation will be assessed using a brief weekly online survey (Castor EDC, Castor).

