### Questionnaires

After each measurement visit (ie, baseline, 3, 6 and 12 months postoperatively), participants will receive an email with a personal weblink to an online questionnaire (Castor EDC, Castor) to assess HRQoL and gastrointestinal symptoms and a separate weblink to an online Food Frequency Questionnaire (FFQ tool, Wageningen University and Research, Wageningen, The Netherlands). In addition to the online questionnaires, a brief set of structured questions will be asked in person during each measurement visit. These questions address current engagement in RT (eg, type of exercise and frequency), weekly performance of light, moderate and vigorous PA and prior use of glucagon-like peptide 1 receptor agonists for weight loss.

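### Treatment adherence, which arises after randomisation and is monitored only in the intervention group, is listed as a confounder to be added to the treatment-comparison model; it should come off that list

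*Protocol article*

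**What the plan says.** All references are to the protocol article.

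- **Statistical analysis.** On the main analysis: "For the primary analysis, an intention-to-treat approach will be used". The models are generalised estimating equations for dichotomous outcomes and linear mixed models for continuous ones. After the effect-modification rules, a further step is added: "confounding will be evaluated for sex, age, baseline BMI, treatment adherence and type of surgery by including each variable in the model separately". The section does not define the adherence variable, and does not say what follows if adding a variable changes the treatment estimate.
- **Protocol adherence.** "For participants in the intervention group, adherence to the RT protocol will be monitored via the Technogym application". The same paragraph adds a single-question survey on home training and two further sources: "Attendance at the supervised RT sessions will be recorded using an attendance list" and "Adherence to the whey protein supplementation will be assessed using a brief weekly online survey". Supervised sessions and the trial whey are provided only to the intervention group.
- **Intervention.** The programme runs "starting 3 weeks after surgery and continuing for a total of 24 weeks", so adherence to it can only arise after allocation.
- **Standard care.** "Allocation to our control group does not restrict participants from engaging in RT or consuming additional protein". No adherence variable is defined for controls.

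**The concern.** A confounder of a treatment comparison must influence, or share a cause with, who receives which treatment. Here a random process decides that. Adherence to the programme is produced by allocation and then helps to produce the outcome. Conditioning on it does not correct a bias; it changes the question and can introduce a bias.

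There is also a practical fault. A variable recorded in one arm only is either missing for every control or fixed at a constant for every control, and neither lets a regression separate the arm effect from adherence in a useful way.

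At stake is the reading of the result. A step called an evaluation of confounding invites the reader to trust the adjusted figure if it differs from the unadjusted one. For adherence, a large difference is expected even when nothing is confounded.

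**Working it through.** **1. The plan's own figure.** The Sample size section gives 26% v 14%, two-sided α = 0.05, power 80%, 174 per arm. With pooled variance and mean proportion 0.20:

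n = [1.960·√(2·0.20·0.80) + 0.842·√(0.26·0.74 + 0.14·0.86)]² / 0.12² = (1.109 + 0.471)² / 0.0144 ≈ 173.3, rounded up to 174. The figure is reproduced. Recruiting 200 per arm with 10% loss leaves 180 per arm, used below. The planned effect is a log odds ratio of ln[(0.14/0.86)/(0.26/0.74)] = −0.77 (odds ratio 0.46).

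**2. Controls missing.** A complete-case fit drops every control. Among the remaining patients the arm indicator equals the intercept column, so the design matrix (intercept, arm, adherence) has rank 2 of 3. The arm effect is not estimable, whatever the effect size.

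**3. Controls coded 0: loss of precision.** Let adherence in the intervention arm have mean μ and variance σ², with equal arms. The variance inflation for the arm term is VIF = 1 + μ²/(2σ²), and the SE is multiplied by √VIF. For a yes/no variable with proportion p adherent, μ = p and σ² = p(1−p), so VIF = (2−p)/[2(1−p)].

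The documents give no adherence distribution, so every row is an assumption:

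| Assumed adherence in intervention arm | VIF | SE multiplied by |
|---|---|---|
| Yes/no, 60% adherent | 1.4/0.8 = 1.75 | 1.3 |
| Yes/no, 70% | 1.3/0.6 = 2.2 | 1.5 |
| Yes/no, 80% | 1.2/0.4 = 3.0 | 1.7 |
| Yes/no, 90% | 1.1/0.2 = 5.5 | 2.3 |
| Continuous, mean 0.75, SD 0.20 | 1 + 0.5625/0.08 = 8.0 | 2.8 |
| Continuous, Beta(5.6, 2.4), mean 0.70, variance 0.0233 | 1 + 0.49/0.0467 = 11.5 | 3.4 |

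One simulated data set under the last row gave a VIF of 12.6.

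The table uses the linear-model formula. In a logistic model the intervention arm carries less information (0.14·0.86 = 0.120 v 0.26·0.74 = 0.192 per patient). For the last row, with the effect unrelated to adherence:

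- unadjusted variance = 1/(180·0.192) + 1/(180·0.120) = 0.029 + 0.046 = 0.075, SE 0.27;
- adjusted variance = 0.075 + (0.49/0.0233)·0.046 ≈ 1.04, SE 1.02, a ratio of about 3.7.

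**4. Controls coded 0: what the coefficient estimates.** Logistic models at 3 months, 180 per arm, simulated:

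| Scenario | Adherence assumed | Arm log OR (SE), without adherence | With adherence | Rejection, without → with |
|---|---|---|---|---|
| 26% v 14%, effect acts through adherence | mean 0.75, SD 0.20 | −0.78 (0.28) | −0.05 (0.80) | 81% → 4% |
| Same | Beta, mean 0.70 | −0.76 (0.28) | +0.08 (0.99) | 80% → 4.6% |
| 26% v 14%, effect unrelated to adherence | Beta, mean 0.70 | −0.77 (0.28) | −0.72 (1.04) | 83% → 8.5% |
| No treatment effect, adherence only prognostic (assumed log OR −2 per unit) | Beta, mean 0.70 | +0.03 (0.24) | +1.44 (0.80) | 4.9% → 45% |

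The first row rests on 1,000 simulated trials and the others on 1,500 each. For the third scenario under mean 0.75, SD 0.20, the adjusted SE was 0.87 and rejection 11%.

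The last row can be checked by hand: extrapolating from mean adherence 0.70 to zero shifts the arm coefficient by −2 × (0 − 0.70) = +1.4. The false signal there is towards apparent harm.

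**The case against.** The strongest reply is that the trial's main result is safe. Intention to treat is stated for the primary analysis, the confounder step comes afterwards as an addition, and each variable is entered on its own. A reader might infer that the plan removes or makes inestimable the effect the trial is run to estimate, or that it contradicts intention to treat. The documents do not support either reading: no sentence lets an adjusted model take the place of the primary one, and a poorly interpretable supplementary model does not contradict a statement about the primary analysis. A reader might also infer that the adjusted figure would be reported as proof of confounding. The plan has no retention or reporting rule for confounders, so that is a prediction; and such a rule may sit in a fuller document that is not shown.

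A second reply is that a measure in both arms could be built. Standard care also recommends home resistance training two to three times weekly. The in-person visit questions are not restricted by arm ("These questions address current engagement in RT (eg, type of exercise and frequency"), and dietary intake is collected by questionnaire at each follow-up. This makes the results on missing or zero-coded controls conditional on using the adherence data that the plan describes. It does not rescue the list: training and protein intake during follow-up would still be post-randomisation and on the causal path.

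A third reply is that the size depends on assumptions. That stands: the loss of precision is modest for a yes/no variable at 60% adherent and large for a continuous one, and the simulations use a single time point where the plan has a repeated-measures model.

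What remains is the listing itself. For effect modifiers the section says that stratified results accompany the overall ones; for confounders it gives no such assurance, and nothing marks the adherence model as exploratory.

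**Conclusion.** The listing is wrong as written and should be fixed. Adherence cannot confound this randomised comparison, and that conclusion needs no numerical assumption. Nor does the failure of estimation when controls have no value.

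If controls are coded 0, the size depends on the assumed adherence distribution: the SE is about 1.3 to 3.7 times larger. The estimate moves to about zero if the effect acts wholly through adherence, stays near the truth but is very imprecise if the effect is unrelated to it, and gives a 45% false-positive rate in the one prognostic scenario examined.

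The fault lies in a supplementary model. The primary endpoint, the intention-to-treat estimate and the sample size stand, provided the adherence-adjusted model is not used to replace or qualify the primary result. The text does not say that it will be, but does not exclude it.

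**What to change.** Delete treatment adherence from the confounder list and keep only baseline variables there.

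If the effect in patients who follow the programme is of interest, pre-specify it separately, in one of two ways:

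- a complier-average causal effect with allocation as the instrument, with adherence defined in advance and the assumption stated that allocation affects the outcome only through the adherence so defined; or
- a description of outcome by adherence within the intervention arm, labelled non-randomised.

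The cost is wording in the protocol and analysis plan. No extra data, patients or change to the primary model are needed. Recruitment is expected to continue until December 2026, so the change can be made before the outcome data are analysed.
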